## **1 - Definition of the research problem and relevant literature**

The exponential growth in extreme heat events subsequent to global climate change is leading to increasing heat related morbidity and mortality around the world [1-5]. The impact, whilst global, is unevenly distributed, with certain demographics suffering much more than others during heatwaves. Those with low socio-economic status are one such demographic [6].

Paradoxically, the presence of, and capacity to afford, air conditioning inside the home decreases risk of ill-health during heatwaves significantly [6] whilst increasing energy usage markedly, thereby further contributing to global climate change [7]. Conversely, those without an air-conditioner, or who are unable to afford to turn it on suffer worse during heatwaves, and must rely on low-cost, and often inadvertently low-emission, cooling interventions. One such intervention that consumes ~45 times less power than air conditioning is the electric fan [8]. However, national [9, 10] and global groups, including the World Health Organisation [11] still advise avoiding electric fan use in environments where ambient temperature exceeds skin temperature ( $\sim 35^{\circ}\text{C}$ ), stating that in these settings they exacerbate strain, in spite of recent evidence dispelling this common belief [12].

Contrasting the stigma surrounding fan use in the heat is the recent work of Morris et al. [12] which demonstrated that fan use can mitigate cardiovascular strain, whilst not worsening thermal strain in ambient temperatures of  $40^{\circ}\text{C}$ . Morris et al. [12] demonstrated the relationship between humidity and the effectiveness of fan use, as strain was worsened by fan use in very dry conditions but mitigated in more humid environments. This research has laid the foundation for global change in the advice given to the public about electric fan use during heatwaves by dispelling the myth that there is a critical temperature beyond which fans stop working. However, there are still concerns about the use of fans when coupled with dehydration which must be addressed in order to confirm utility of electric fans in real life heatwave contexts, during which mild dehydration may be present. In the work of Morris et al. participants were euhydrated throughout [12].

Fundamentally, fans off-set thermal strain by increasing the rate at which sweat evaporates from the skin surface, which is our best heat dissipation mechanism [13]. In dry environments, sweat already evaporates readily; this is why fans are not helpful in dry heatwave simulations, but in humid contexts, sweat does not evaporate as readily, therefore the assistance given by

the forced airflow of an electric fan mitigates thermal strain [12]. Dehydration can cause reductions in sweat output, which may reduce or even reverse the advantage of fan use [14]. If air warmer than the skin surface is forced over dry skin (subsequent to dehydration related decrements in sweat output) it may lead to convective heat gain, which would in fact worsen thermal strain.

The degree of sweat output reduction is directly related to the level of dehydration; it is as yet unknown whether the amount of dehydration which may occur in a heatwave (~2-3% total body weight) causes a significant enough reduction in sweat rate to impact the utility of electric fan use and if so, how great this impact is. Ultimately, it is important to understand this relation as it may impact public health guidance surrounding electric fan use in heatwaves. It is therefore the aim of this study to quantify the effect of a realistic level of dehydration on electric fan utility during an extreme heat event with a view towards informing publicly available heatwave advice.

## 2 - Objectives and evaluation criteria

### 2.1. Primary objective

To examine whether dehydration modifies the effect of electric fan use on thermal and cardiovascular strain, and thermal comfort during a 3-h exposure to a simulated peak hot-humid heatwave condition.

### 2.4 Outcome variable summary

| Outcome variable                           | Analysis timepoint(s)                                                                |
|--------------------------------------------|--------------------------------------------------------------------------------------|
| Rectal temperature (°C)                    | End of heat exposure (average of last 5-min of 3-h heat exposure)                    |
| Heart rate (beats·min  )      | End of heat exposure (average of last 5-min of 3-h heat exposure)                    |
| Whole-body sweat rate (g·h  ) | Cumulative total sweat loss during heat exposure divided by total heat exposure time |
| Thermal sensation (mm)                     | Final rating at end of heat exposure                                                 |
| Thermal discomfort (mm)                    | Final rating at end of heat exposure                                                 |
| Thirst (mm)                                | Final rating at end of heat exposure                                                 |

### **3 - Methods**

#### *3.1 Study design*

A repeated measures (crossover) design study requiring all participants to complete one 5-day 'hydration baseline' period, followed by four 3-h passive heatwave exposures (counterbalanced using balanced Latin square design), two whilst well hydrated, two hypohydrated, both with and without an electric fan. Experimental trials will be separated by at least 96 h, and all preceded by a 24-h period of carefully prescribed fluid consumption that will ensure either euhydration or contribute to the development of moderate hypohydration. A crossover design was selected because the lower within-person variation in the human heat stress response compared to between individuals enables better statistical power for the detection of between-condition effects.

##### Hydration baseline:

To contextualize changes in hydration status throughout the study each participant will undergo a 5-day hydration baseline immediately preceding their first experimental trial. A minimum of 3 d monitoring has previously been demonstrated to provide a valid indication of typical daily body mass fluctuations [15]. The hydration baseline involves collecting a first pass, mid-stream urine sample which will later be used for the purposes of urine specific gravity (USG) analysis with a refractometer (Atago, Japan), as well as a nude body mass measurement with an empty bladder, immediately after waking. Participants will be provided with a portable platform scale (KW4050, @weigh, Australia) and carry out this data collection at the same time of day each morning after waking for 5 days. All urine samples will be stored at 4°C for no more than 48 h before analysis [16].

##### Main experimental trials:

Following a 5-day hydration baseline, participants will be asked to complete four 3-h passive heatwave exposures (39°C, 50% relative humidity) with all trials separated by a minimum of 4 days, to eliminate any carryover effects, and completed within a 3-week span to ensure no discernible difference in heat acclimatization status. All experimental trials are scheduled to start at 0800 h, with participants twice asked to adhere to a 'high fluid intake' and twice to a 'low fluid intake' protocol in the 24 h leading up to the experimental visit. The aim of the high fluid intake protocol is to ensure the participant arrives well hydrated for their experimental

visit. Based on the work of Armstrong and Johnson (2018) detailing daily fluid requirements of men and women [17], female participants were asked to consume 1.8-2.1 L, and male participants 2.4-2.8 L of water throughout the day before their two euhydrated trials, as well as ~500 ml of water alongside a light meal in the 2 h leading up to the trial. The low fluid intake protocol requires participants to consume no water or any other drink during the 24 h leading up to their two hypohydrated trials, as well as the avoidance of food products with >75% water content, a protocol that has previously resulted in a 24-h body mass reduction of ~2% [18].

In advance of all experimental trials, participants will also be asked to abstain from caffeine and alcohol and to avoid strenuous physical exertion for 24 h. Additionally, participants will be asked to maintain a food diary throughout their first high and low fluid intake protocols and replicate them the second time they undergo each protocol.

The four experimental trials differ firstly in hydration status upon arrival and throughout (euhydrated or hypohydrated) and secondly via the employment of an electric fan, placed 1.5 m from the participant provided constant forced airflow of 2.5 m/s (measured 1.5 m away from the fan) throughout the exposure, equivalent to the high setting on a commercially available pedestal fan. The four experiment trials are therefore:

- (1) Euhydration, No-Fan (EUH-NF)
- (2) Euhydration, Fan (EUH-FAN)
- (3) Hypohydration, No-Fan (HYP-NF)
- (4) Hypohydration, Fan (HYP-FAN).

To maintain hydration status throughout the euhydration trials, participants will receive either 2.5 ml/kg (EUH-NF) or 3.5 ml/kg (EUH-FAN) of 37°C water at the 30, 60, 90, 120 and 150-min marks. A greater amount of water is given in the EUH-FAN trial to offset the greater sweating output associated with fan use, compared to no fan, that has been previously observed [12, 19]. No water will be provided or consumed during hypohydration trials.

### *3.2 Description of the population*

To complete this study, young healthy participants (non-smokers with no history of respiratory, metabolic, cardiovascular, blood pressure disease, or of diabetes and not currently on any medication) between the ages of 18 and 40 will be recruited.

### *3.2.1 Inclusion/Exclusion criteria*

**Age:** All participants must be between 18 and 40 years old.

**Medication:** Participants must not be currently taking any medication.

**Disease History:** Participants must not currently have or have had in the last 24 months a respiratory (e.g. COPD, severe asthma), kidney (e.g. kidney disease, acute kidney injury) or metabolic disease (e.g. diabetes, endocrine disorders). Participants must have no history of cardiovascular disease.

**Smoking status:** Participants must have been non-smokers for >24 months prior to participation in this study.

**Fear of needles (trypanophobia):** Participants with trypanophobia will be excluded as insertion of the rectal temperature probe may elicit a similar response.

### *3.2.3 Strategy for recruiting and retaining participants in the study*

To recruit participants, a recruitment flyer has been created. This flyer will be printed out and posted around/ circulated at the University of Sydney. Further, we intend to circulate information relating to the study on pre-existing Thermal Ergonomics Laboratory social media accounts including Twitter, Facebook, and Instagram. These social media accounts are already active. Specifically, we intend to circulate an infographic which has been edited for better suitability to phones/ tablets/ computers but contains the same information as the printable flier.

The researchers' contact information will be on these flyers and those individuals who may be interested in participating can contact the researchers at their own discretion.

Initial contact will be made when the participants phone or email the researchers. As such, the opportunity for coercion is minimized. Upon receiving initial contact, a standardized email will be sent to the potential participant: i) outlining inclusion/exclusion criteria; ii) providing an outline of the study details with an attached Participant Information Sheet; iii)

inviting the participant to schedule preliminary visit to learn more about the study and provide informed consent.

### *3.3 Measurements*

**Rectal probe:** In order to monitor the amount of heat stored in the body the participant will be asked to insert a thin, flexible temperature probe ~12 cm into their rectum. Complete written instruction will be given to the participants on the placement of the rectal probe to ensure their safety and comfort. In brief, they will be asked to place a marker ~12 cm from the tip of the probe using sterile surgical tape. They will then insert the probe until the tape reaches their anal surface. On occasion, the insertion of the probe may cause some mild discomfort and minor irritation; however, this sensation passes within 5 minutes. The participant will be responsible for the insertion of this probe.

**Heart rate:** Measures of heart rate will be recorded continuously using a two-channel chest band (Polar, Kempele, Finland).

**Whole-body sweat loss (WBSL):** The participant will be weighed on a platform scale nude in triplicate at baseline, and immediately after the exposure to determine whole body sweat loss.

**Resultant dehydration (%DEH):** Will be calculated using pre and post body masses.

**Whole-body thermal sensation (WBTS):** During the trial participants will be asked, every 20 minutes, to rate their whole-body thermal sensation on a 100 mm visual analogue scale that ranks from very cold (like touching an ice cube) to very hot (hottest they have ever felt).

**Thermal discomfort:** During the trial participants will be asked, every 20 minutes, to rate their thermal comfort on a four-point visual analogue scale which ranges from not uncomfortable to very uncomfortable.

**Rating of Thirst:** During the trial participants will be asked to rate their thirst, every 20 minutes, on a visual analogue scale. This scale consists of 3 questions:

- (i) How thirsty do you feel right now?
- (ii) How dry does your mouth feel right now?
- (iii) How pleasant would it be to drink some water right now?

For each of these questions' participants mark anywhere on a 100 mm line giving a score out of 100 for each question.

## **4 - Statistics**

### *4.1 Sample size*

To complete this study, we plan to recruit at least 16 young healthy participants (non-smokers with no history or current respiratory, metabolic, and cardiovascular illness/disease, high blood pressure, or diabetes, and not currently on any medication. Male/female participants between the ages of 18 and 40 will be recruited. The number of participants was selected by performing a power calculation using an  $\alpha$  of 0.05, a  $\beta$  of 0.1, an effect size of 0.78 calculated from the differences in change in rectal temperature between euhydrated and mildly (1.9% total body weight) dehydrated individuals across a three hour heatwave simulation [14].

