### *4.2 Statistical analysis*

The effect of hydration (euhydrated/dehydrated) on the influence of fan use (on/off) for all outcomes will be assessed using a Linear Mixed Model analysis with Sidak post-hoc testing.

Specifically, we will use a restricted maximum likelihood (REML)-based linear mixed model, accounting for repeated measures, including a term for hydration status (euhydrated, dehydrated), a term for condition (no fan use, fan use), and interaction term between hydration status and condition. This model will be used to compare end-trial values in the primary outcome variables: rectal temperature, heart rate, and whole-body sweat rate, and the secondary outcome variables: thermal sensation, thermal discomfort and thirst. Any missing data will be handled under the Missing At Random (MAR) assumption without listwise deletion. This allows the retention of participants who have missing data in one or more conditions. All available data will be used in the estimation of fixed effects.

The significance threshold is set at  $P=0.05$ . SPSS Statistics (v29.0.1) will be used for all statistical analysis.

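### The sample size of 16 omits the test, sidedness and type of effect size; read as a paired standardized difference, it gives 90% power one-sided but about 83% two-sided

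*Protocol*

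**What the plan says.** Protocol section 4.1 (Sample size) states "we plan to recruit at least 16 young healthy participants". The inputs are an alpha of 0.05, a beta of 0.1 (90% power) and "an effect size of 0.78 calculated from the differences in change in rectal temperature". The comparison behind that effect size is one of hydration alone, taken from an earlier heatwave study with about 1.9% dehydration. The section does not name the test, say whether alpha is one- or two-sided, or say whether 0.78 is scaled by the SD of within-person differences or by a raw SD.

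Section 3.1 describes the design as a crossover in which each participant undergoes all four hydration-by-fan conditions.

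For the analysis, section 4.2 (Statistical analysis) says "we will use a restricted maximum likelihood (REML)-based linear mixed model, accounting for repeated measures". The fixed effects are hydration, fan use and their interaction, with Sidak comparisons afterwards, and significance is judged at P=0.05. No one-sided test is mentioned. The primary objective in section 2.1 asks whether dehydration changes the fan's effect and gives no direction.

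**The concern.** Section 4.1 states alpha, beta, effect size and sample size together, so the four should agree under the analysis planned in section 4.2. On the most natural reading for a crossover, they agree only if alpha is one-sided. Tests of fixed effects in a mixed model have no direction unless one is specified. Nor do the aims suggest one: the background in section 1 allows that dehydration may lessen the fan's benefit or turn it into harm.

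At stake is the stated type II risk. If it is about 17% rather than 10% for the contrast used to size the trial, a non-significant result carries less weight than section 4.1 implies. That matters because section 1 says the results are meant to inform public heatwave advice.

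**Working it through.** **Inputs.** From section 4.1: alpha 0.05, beta 0.1, effect size 0.78, n = 16. From section 3.1: every participant completes all conditions, so the comparison is paired. Assumption: 0.78 is dz, the mean within-person difference divided by the SD of those differences.

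**Formula.** Exact power of a paired t-test comes from the noncentral t distribution with df = n − 1 and noncentrality dz × √n. At n = 16 the noncentrality is 0.78 × 4 = 3.12 on 15 df.

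**Step 1: reproduce the stated figure.** One-sided alpha 0.05 (critical t 1.753 on 15 df):
- n = 15: power 0.890
- n = 16: power 0.908

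The smallest n reaching 90% is exactly 16.

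**Step 2: the same contrast, two-sided.** Two-sided alpha 0.05 (critical t 2.131 on 15 df):
- n = 16: power 0.830, so type II risk is 1 − 0.830 = 0.170
- n = 19: power 0.895
- n = 20: power 0.911

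The smallest n reaching 90% is 20. At n = 16, the effect detectable with 90% power is dz = 0.87.

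**Step 3: could another standard calculation give 16?**
- *Two-sided normal approximation.* ((1.960 + 1.2816)/0.78)² = 17.3, rounded up to 18. Power at 16 is 0.877. This is optimistic at so small a sample and still below 0.90.
- *Pooled mixed-model degrees of freedom.* Four observations on each of 16 participants give 15 × 3 = 45 df. Two-sided power with noncentrality 3.12 is 0.863.
- *Independent groups (normal approximation).* 29 per group one-sided, 35 two-sided. Neither is near 16.
- *0.78 as a raw-SD effect size.* Then dz = 0.78/√(2(1 − ρ)), where ρ is the within-person correlation:

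| Assumed ρ | dz | Two-sided power, n = 15 | Two-sided power, n = 16 | n for 90% |
|---|---|---|---|---|
| 0.5 | 0.780 | 0.802 | 0.830 | 20 |
| 0.6 | 0.872 | 0.881 | 0.903 | 16 |
| 0.7 | 1.007 | 0.952 | 0.964 | 13 |

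A correlation of about 0.6 therefore also reproduces 16, two-sided. The protocol gives no correlation.

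**Step 4: what the 83% covers.** It is the power of one paired hydration contrast, not of the terms in the 2×2 model.
- *Hydration main effect.* This averages two hydration differences per participant. If each has dz 0.78 and they correlate at c, the averaged contrast has dz = 0.78 × √(2/(1 + c)). Two-sided power at n = 16 is 0.984 (c = 0), 0.920 (c = 0.5), 0.903 (c = 0.6), 0.885 (c = 0.7) and 0.830 (c = 1). The protocol does not give c.
- *Hydration-by-fan interaction.* Suppose, for illustration only, an interaction of the same raw size as the hydration difference and independent errors. The contrast then has dz = 0.78/√2 = 0.552, and power at n = 16 is 0.541 on 15 df or 0.579 on 45 df.

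**The case against.** The strongest objection is that section 4.1 never calls 0.78 a paired dz. If it is a raw-SD effect size and the correlation is about 0.6, 16 is the correct two-sided answer and nothing was miscalculated. This stands. A reader might infer that 16 can arise only from a one-sided test, or that a one-sided test was certainly used. The document supports neither: the one-sided origin is an inference from an exact match under an assumed effect-size type.

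The second objection is that 83% is not the power of the planned mixed model. This stands too. A reader might conclude that the model's hydration test falls short of 90%. That is not shown, because the main effect could have power from 0.83 to above 0.98, depending on a correlation the protocol does not state.

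The third is that the plan sets a minimum of 16, and that an analysis plan not at hand may state the sidedness. A minimum does allow more recruits, but section 4.1 attaches the 90% to 16. The point is also not just missing detail: on the natural reading, the stated figures do not agree with the non-directional tests in section 4.2, and on the alternative reading they rest on an undisclosed input.

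The larger issue, that 0.78 describes hydration alone while the objective concerns the interaction, is not answered by any of this. A corrected power statement must not obscure it.

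**Conclusion.** The point holds in conditional form. If 0.78 is a paired standardized difference and the test is two-sided at 0.05, 16 participants give 83% power for a single euhydrated-versus-dehydrated contrast on 15 df, or about 86% on 45 pooled df. The stated figure is 90%, which would need 20 participants with the paired t-test. The type II risk is then about 17% (14% with pooled df) rather than 10%, before any loss of participants.

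The stated 90% can be right for one two-sided contrast, but only with an input absent from the protocol, for example a raw-SD effect size with a correlation of about 0.6. As written, the two-sided 90% cannot be verified. None of these single-contrast figures is the power for the hydration-by-fan interaction.

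**What to change.** Restate the power sentence in section 4.1 along these lines:

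> If 0.78 is a paired standardized difference, 16 participants give about 83% power for a single euhydrated versus dehydrated contrast (paired t-test, two-sided alpha 0.05); the effect detectable with 90% power is dz = 0.87. This figure is not the power for the hydration-by-fan interaction.

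State in section 4.1 which type of effect size 0.78 is and any within-person correlation used. If it proves to be a raw-SD effect size, give the correlation and recompute the power from it. Add to section 4.2 that all tests are two-sided.

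The cost is a few sentences. On the paired reading, the stated power falls from 90% to about 83%. No added participants are required; if the sponsor prefers to keep 90% two-sided on that reading, this contrast needs 20.

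### The sample size is calculated for a hydration contrast, while the primary objective is the hydration-by-fan interaction, for which the protocol gives no effect size or power

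*Protocol*

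**What the plan says.** Protocol 2.1 states the primary aim: "To examine whether dehydration modifies the effect of electric fan use on thermal and cardiovascular strain", together with thermal comfort, over a 3-h hot-humid exposure. Section 3.1 sets a within-person crossover of four trials, crossing hydration (euhydrated, hypohydrated) with fan (off, on).

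Section 4.2 repeats the target as "The effect of hydration (euhydrated/dehydrated) on the influence of fan use (on/off) for all outcomes". It fits a REML linear mixed model with terms for hydration, fan condition and their interaction. End-trial rectal temperature, heart rate and whole-body sweat rate are the primary outcomes. "The significance threshold is set at" 0.05, and sidedness is not given.

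On size, section 4.1 says "we plan to recruit at least 16 young healthy participants". "The number of participants was selected by performing a power calculation using an" alpha of 0.05 and a beta of 0.1, with "an effect size of 0.78 calculated from the differences in change in rectal temperature between euhydrated and mildly" (1.9% of body weight) "dehydrated individuals across a three hour heatwave simulation". It does not say whether the test is one- or two-sided, or which SD standardises the 0.78. It mentions neither a fan effect nor an interaction.

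**The concern.** The only power statement answers a different question from the primary objective. A hydration contrast compares two conditions. The interaction is a difference of two differences over four conditions: (HYP-FAN − HYP-NF) − (EUH-FAN − EUH-NF). With equal, exchangeable within-person errors it has twice the variance of a simple difference. Its true size is also a separate quantity, which the protocol does not estimate.

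A reader of 4.1 would take the trial to have 90% power for its main question, and nothing in the protocol supports that. The background section says the results are meant to inform public heatwave advice. If the real power is much lower, a non-significant interaction would be a common result even when dehydration materially alters the benefit of a fan, and it should then carry little weight as reassurance.

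**Working it through.** **Inputs.** From 4.1: alpha 0.05, beta 0.1, effect size 0.78, n = 16. From 3.1: each participant completes all four conditions.

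**Assumptions, not in the protocol.** The 0.78 is d_z (mean paired difference divided by the SD of paired differences). It carries over to the end-trial value that 4.2 analyses. The SD of the hydration difference is the same with and without fan.

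**Step 1: reproduce the plan's figure.** Paired t-test, noncentral t with n − 1 df and noncentrality d_z·√n = 0.78 × √16 = 3.12.

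| Test | Power at n = 16 | n for 90% |
|---|---|---|
| One-sided 0.05 | 90.8% | 16 |
| Two-sided 0.05 | 83.0% | 20 |

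The stated 16 matches the one-sided paired test. A comparison of independent groups does not reproduce it (29 per arm one-sided, 35 two-sided).

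**Step 2: the interaction.** With error variance σ² per condition, a simple difference has variance 2σ² and the double difference 4σ², so its SD is √2 times larger. This is the same as taking the two hydration differences (with fan, without fan) to be independent. For an interaction equal in size to the hydration effect:

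d_z = 0.78/√2 = 0.552, noncentrality 0.552 × 4 = 2.21.

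| Test | Power at n = 16 | n for 90% |
|---|---|---|
| One-sided | 67.7% | 30 |
| Two-sided | 54.1% (57.9% with 45 error df) | 37 |

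**Step 3: vary the interaction size.** d_z = f × 0.552, two-sided, n = 16, where f is the interaction relative to the hydration effect.

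| f | 0.5 | 0.75 | 1 | 1.25 | 1.5 |
|---|---|---|---|---|---|
| Power | 18% | 34% | 54% | 73% | 87% |

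Ninety percent two-sided needs d_z = 0.868, that is f = 0.868 × √2/0.78 = 1.57.

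**Step 4: vary the correlation r between the two hydration differences.** d_z = 0.78/√(2(1 − r)), f = 1, two-sided, n = 16.

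| r | −0.25 | 0 | 0.25 | 0.5 |
|---|---|---|---|---|
| d_z | 0.493 | 0.552 | 0.637 | 0.780 |
| Power | 45% | 54% | 66% | 83% |

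**Step 5: vary the scaling of 0.78.** If it is standardised by a between-person SD, the paired d_z is 0.78/√(2(1 − ρ)), with ρ the within-person correlation, and the interaction d_z is that divided by √2. For f = 1, two-sided, n = 16, power is 31% at ρ = 0, 54% at ρ = 0.5, 76% at ρ = 0.7 and 90% at ρ = 0.8.

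**The case against.** The strongest reply is that 54% rests on inputs the protocol does not supply, and this stands. A reader might infer that 54% is the most the trial can achieve. The documents do not support that: the background section allows that dehydration could reverse the fan's advantage, so an interaction larger than the hydration effect is not excluded, and a positive correlation between the hydration differences also raises power (steps 3 and 4).

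A reader might also set 90% against 54% and call that the loss. Those figures mix sidedness. Like for like, the drop is from 91% to 68% one-sided, or from 83% to 54% two-sided.

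Nor does the stated power belong to the model's hydration main effect. Section 4.1 describes a two-condition contrast from an earlier study. Averaging over both fan conditions would halve the variance, giving d_z = 0.78 × √2 = 1.10 and about 98% power two-sided under the same assumptions. It would equally be an inference to say that the earlier contrast was measured without a fan, because 4.1 does not say so.

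Finally, no section says that a non-significant interaction will be read as no effect. The background frames the aim as quantifying the effect, 16 is a floor, and reporting detail may sit in an analysis plan that is not shown. This softens the stated harm. It does not remove the mismatch, because 4.1 itself gives the basis for the number and that basis is not the primary question.

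**Conclusion.** The concern holds in this form: the alpha, beta and effect size in 4.1 belong to a simple hydration contrast, and the protocol offers no effect size or power for the interaction that 2.1 and 4.2 make primary. That much rests on the text alone.

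The size of the shortfall is conditional. With 0.78 as a paired d_z, an interaction equal to the hydration effect and independent hydration differences, power at 16 is about 54% two-sided or 68% one-sided. Across the two-sided ranges examined it runs from 18% to 87% by interaction size, 45% to 83% by correlation, and 31% to 90% if 0.78 is scaled to a between-person SD. The implied 90% for the primary question is therefore unsupported rather than shown to be unattainable. Separately, 16 gives 90% even for the hydration contrast only if the test is one-sided.

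**What to change.** **Section 4.1.** State that the 0.78 calculation concerns a hydration contrast and not the interaction. Give its sidedness and the SD by which 0.78 is standardised. Replace the implied 90% with the interaction's power on the same sidedness as the analysis. For a two-sided test: 16 participants give 90% power for an interaction of about 0.87 of its own contrast SD, and about 54% for one equal to the hydration effect, given a paired-difference scale and independent hydration differences. Show the range around that figure.

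**Section 4.2.** Report the interaction estimate with its 95% CI as the primary result for rectal temperature, heart rate and sweat rate. State that P > 0.05 for the interaction will not be interpreted as absence of effect modification.

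**Cost.** Wording in two sections and no additional participants. The downside is a less favourable stated power.
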